## Abstract

**Background:**

Given the limited research focusing on psychotherapeutic interventions for suicide attempters, it is noteworthy that the Attempted Suicide Short Intervention Program (ASSIP) has demonstrated promising results in previous studies. In this investigation, we aim to evaluate the effectiveness of ASSIP across diverse healthcare settings, outlining the study design and planned evaluation.

**Methods:**

Using a Randomized Controlled Trial (RCT) design with four assessment points (baseline, 3, 12- and 24-month follow-up), we aim to assess the effect of the 3-session psychotherapeutic intervention and hereafter brief contact via structured letters during 2 years in a clinical sample of recent suicide attempters (suicide attempts within three months before inclusion). Participants are randomly assigned to one of two groups; treatment as usual plus ASSIP or the control condition, treatment as usual. Assessments include measures of suicidal intent, coping, symptoms of depression, quality of life, self-stigma, and sick leave. The primary outcome is suicide attempt(s) within 3, 12, and 24 months and the secondary outcome is suicidal ideation within the same time frames after study inclusion.

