In a randomized controlled trial (RCT) conducted in Switzerland [17], 60 patients receiving ASSIP in addition to standard care exhibited an 80% risk reduction for new suicide attempts within two years compared to the control group. Health economic benefits were observed [18]. However, a Finnish study [19] comparing ASSIP with crisis intervention demonstrated no discernible difference in effectiveness, which the authors potentially attributed to methodological limitations and the high prevalence of personality disorders among participants [19]. A small pilot RCT from the US [20] focusing on individuals with extensive substance abuse problems and suicide attempts, reported no difference in repeated suicide attempts but a reduction in suicidal thoughts with an adapted form of ASSIP treatment compared to standard care. Notably, the healthcare context appears to influence intervention outcomes. While ASSIP displays promising results, replication studies in diverse international contexts are hindered by methodological challenges. Comprehensive investigations, encompassing treatment fidelity, usual care content, and patient selection criteria, are warranted to determine the effectiveness of ASSIP in preventing new suicidal behaviors.

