### Power calculation

Based on Swiss findings regarding the effect of ASSIP [17], we anticipate that 10% of individuals in the group receiving ASSIP plus conventional treatment, and 20% of individuals receiving conventional treatment alone, will attempt suicide again during the follow-up period. According to the chi-square test, 199 individuals are required in each group to achieve a significant difference with a power of 0.8 and an alpha value of 0.05. Assuming a 15% dropout rate among patients, 460 patients need to be recruited. If the dropout rate is lower, fewer patients will suffice.

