### Statistical considerations

The chi-square test will be utilized to assess differences between the intervention group and the control group regarding the main outcome. The Wilcoxon signed-rank test is planned to be used to analyze significant changes over time, and the Mann-Whitney U test for differences between groups. To visually represent the cumulative probability of suicide reattempt over time in each treatment group, we plan to create Kaplan-Meier curves. Simple and multiple logistic regression to compare the relative impact of different factors on the outcome. Data regarding the professions and previous psychotherapeutic training of therapists will be collected and investigated as putative moderators. Further, we plan to employ cost calculation items for assessing direct and indirect costs, and total costs for the cost-effectiveness model.

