### Reporting and publication plan

In accordance with the Declaration of Helsinki, study results will be made publicly available, through publication and/or a public database as soon as possible after the study is completed. This applies regardless of whether the results are positive, negative, or neutral. The first main outcome study will provide preliminary results after a one-year follow-up is completed for the last participant included in the RCT.

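### Three nested windows are all primary with none decisive, and the single power calculation does not say which window it covers

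*Protocol article*

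**What the plan says.** - **Outcome.** Abstract, Methods: "The primary outcome is suicide attempt(s) within 3, 12, and 24 months". The Outcomes section of the main text names new suicide attempts as the primary outcome variable and lists the data sources, but does not choose a window.
- **Sample size.** Power calculation: "we anticipate that 10% of individuals in the group receiving ASSIP plus conventional treatment, and 20% of individuals receiving conventional treatment alone". These are the proportions expected to make a further attempt, and the only timing given for them is that they "will attempt suicide again during the follow-up period". No month is attached. The result is that "199 individuals are required in each group to achieve a significant difference with a power of 0.8 and an alpha value of 0.05", and then "Assuming a 15% dropout rate among patients, 460 patients need to be recruited". The rates are said to rest on the Swiss trial, which the Background describes as showing an "80% risk reduction for new suicide attempts within two years compared to the control group".
- **Test.** Statistical considerations: "The chi-square test will be utilized to assess differences between the intervention group and the control group regarding the main outcome". This describes one outcome and one test, with no time point.
- **First report.** Reporting and publication plan: "The first main outcome study will provide preliminary results after a one-year follow-up is completed for the last participant included in the RCT".

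**The concern.** One test and one power figure belong to one hypothesis, but the outcome they serve has three versions. Attempts by 3 months are included in attempts by 12 months, and those in attempts by 24 months. The three comparisons are therefore correlated but not identical, and they can disagree. If the arms differed significantly at 12 months and not at 24, the article gives no basis for calling the trial positive or negative.

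Two things are at stake. First, with three windows carrying the primary label, the decisive one could be chosen after the data are seen. The Outcomes section also has the research team carry out periodic interim analyses of effectiveness, so the team may see comparative results before the choice is made. Second, the first main paper appears at one year. If the planning rates describe two years, fewer attempts will have occurred by then, and a reader who applies the stated 80% power to that paper would be misled.

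**Working it through.** **1. The plan's own figure.** Inputs from the Power calculation: p1 = 0.20, p2 = 0.10, alpha 0.05 (sidedness not stated, taken as two-sided), power 0.80. With the pooled-variance formula and no continuity correction:

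n = [1.960 × √(2 × 0.15 × 0.85) + 0.8416 × √(0.20 × 0.80 + 0.10 × 0.90)]² / 0.10² = (0.990 + 0.421)² / 0.01 ≈ 199 per group.

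The stated 199 is reproduced exactly (a one-sided test would need 157). For dropout, 398/0.85 gives 469 and 398 × 1.15 gives 458, both close to the stated 460. If 15% of 460 are lost, 391 remain, or about 195–196 per arm. If none are lost, there are 230 per arm.

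**2. False-positive rate if any window could count.** Under no effect, the chi-square statistics at two nested windows with cumulative risks p_i < p_j have correlation √[p_i(1 − p_j) / (p_j(1 − p_i))]. Example: with a 24-month risk of 15%, and 12.5% and 50% of attempts by months 3 and 12 (close to a constant hazard), the risks are 0.01875, 0.075 and 0.15. The correlations are 0.49 (3 with 12 months), 0.33 (3 with 24) and 0.68 (12 with 24).

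The chance that at least one statistic exceeds 1.96 in absolute value was found with 1,000,000 multivariate-normal draws and checked by multinomial simulation at 199 per arm. The article gives no timing of attempts, so the shares below are assumptions. Ranges cover 24-month risks of 15% and 20%. The last column is from the multinomial simulation.

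| Share of attempts by month 3 / month 12 | Any of three windows | 12 or 24 months only |
|---|---|---|
| 10% / 40% | 12.7% | 8.8–8.9% |
| 12.5% / 50% (about constant hazard) | 12.3% (simulation 12.0%) | 8.4–8.5% |
| 25% / 60% | 11.5–11.6% | 8.1% |
| 25% / 70% | 11.3–11.4% | 7.7–7.9% |
| 40% / 75% | 10.5–10.6% | 7.4–7.7% |
| 50% / 80% | 10.0% | 7.3–7.4% |
| 70% / 90% | 8.6% (simulation 8.5–8.9%) | 6.6–6.8% |

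Three independent tests would give 1 − 0.95³ = 14.3%, which is the ceiling. Interim looks at effectiveness are not counted.

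**3. Power at 12 months.** Here 10% and 20% are taken as 24-month rates. Both are multiplied by the share f of attempts that fall in year 1, which keeps the relative risk at 0.5. Power = Φ{[d − 1.960 × √(2p̄(1 − p̄)/n)] / √[(p1(1 − p1) + p2(1 − p2))/n]}, where d = p1 − p2 and p̄ is the mean of the two rates. For f = 0.5 and n = 199, the rates are 0.10 and 0.05, and Φ[(0.05 − 1.960 × 0.02640) / 0.02629] = Φ(−0.07) = 47%.

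| Share in year 1 | 12-month rates | Power, 199 per arm | Power, 230 per arm |
|---|---|---|---|
| 50% | 10% vs 5% | 47% | 53% |
| 60% | 12% vs 6% | 55% | 61% |
| 70% | 14% vs 7% | 62–63% | 69% |
| 75% | 15% vs 7.5% | 66% | 72% |
| 80% | 16% vs 8% | 69% | 75% |
| 90% | 18% vs 9% | 75% | 81% |
| 100% | 20% vs 10% | 80% | 85% |

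For 80% power at 12 months, the number needed per arm is 435 if half of attempts fall in year 1 and 258 if 80% do.

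**The case against.** Several objections are fair.

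- **The error rate is conditional.** A reader might infer that the trial runs a false-positive rate of 11–12%. The article does not support that as a fact. It nowhere says that a win at any window counts, nor that each window is tested at 0.05: that value appears only in the power calculation, and the test is described for a single main outcome. If 24 months alone decided the trial, the error there would stay at 5%. A rule on multiplicity may also sit in an analysis plan that is not shown, so its absence is not the point. What remains is that the article fixes three primary windows and ranks none.
- **The one-year report is called preliminary.** A reader might infer that it is the first confirmatory claim. No section says so. The same sentence, however, calls it the first main outcome study, and the two labels leave its status unclear.
- **The 24-month horizon of the planning rates is an inference.** It rests on the two-year source trial and the two-year follow-up, and is well supported but not stated. Because charts and registers supplement the interviews, a missed interview need not remove a participant. This is why results for 230 per arm are shown. With that number and 90% of attempts in year 1, power does reach 81%.
- **Two further readings do not stand.** The Aims list five primary research questions, but the Outcomes section names one primary outcome variable, so the list does not create five co-primary tests. Nor does the article show that publishing group results at one year would harm the remaining follow-up: participants and therapists know the allocation already, and group results do not reveal an individual's arm to blinded assessors.

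**Conclusion.** The point holds as a defect in how the primary hypothesis is fixed: three windows share primary status, none decides, and the power calculation is tied to an undated period.

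The possible inflation is from 5% to roughly 8.5–12.7%, provided that any window at 0.05 could count and that attempts are timed as in the cases shown. With only 12 and 24 months in play it is about 7–8.5% when 50–80% of attempts fall in year 1.

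The power loss at one year is conditional on 10% and 20% being 24-month rates and on a constant relative risk of 0.5. Within that reading, the stated 80% is missed in every case with 50–90% of attempts in year 1, except the most favourable one with no loss of participants. The sample size itself is correct for the rates given.

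**What to change.** Before any comparative analysis:

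1. Designate one primary window. Twenty-four months fits the source trial and the power calculation. Test it at two-sided 0.05, with 3 and 12 months secondary. Alternatively, state a fixed order in which the windows are tested.
2. State the month to which the 10% and 20% rates and the 80% power apply.
3. State that the one-year preliminary report is a secondary, non-confirmatory analysis.

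The cost is wording in the protocol, the analysis plan and the registry entry. The article says the trial is still recruiting, so this can be settled before the main analysis. The downside is that the 3- and 12-month results lose primary status. Splitting alpha equally over three windows (0.05/3 each) would also remove the ambiguity, but it is expensive: 266 per arm would be needed for 20% versus 10%, and 199 per arm would give only 66% power.

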**Discussion:**

Findings from this study will provide novel insights regarding the effects of ASSIP on not only subsequent suicidal behavior but also other outcomes including self-stigma, quality of life, social network, sick leave, and symptoms of depression.

**Trial registration:**

The trial was registered at ClinicalTrial.gov NCT04746261 on 2020-10-15.

**Supplementary Information:**

The online version contains supplementary material available at 10.1186/s12888-024-06109-z.

## Background

In recent years, the global toll of suicide has exceeded 700,000 fatalities annually, with approximately 1,500 occurrences recorded in Sweden alone [1]. Nearly 11,000 individuals engaged in suicidal behaviors in Sweden in 2021, leading to hospitalization for at least one night or necessitating emergency services [2]. It is crucial to note that the actual prevalence of suicide attempts is likely underestimated, as not all instances come to the attention of healthcare professionals. Estimates suggest that only about half of the true number of suicide attempts receive hospital care in Sweden each year [3]. The gravity of suicide attempts as a risk factor for subsequent suicide is underscored by prior research [4]. Our research group has previously demonstrated that the risk of suicide persists over an extended period following an attempt, and is influenced by psychiatric disorders, suicidal intent, and number of attempts [5, 6]. Recognizing the history of suicide attempts as a high-risk demographic [7], it becomes imperative to prioritize comprehensive assessment, treatment, and ongoing monitoring after a suicide attempt.

In our investigations involving individuals who died by suicide in Sweden in 2015 and had prior contact with psychiatric services, it was revealed that 51% had a history of at least one suicide attempt [8]. Even though some of these individuals were receiving extensive pharmacological and psychological interventions, the persistence of suicidality underscores the inadequacy of existing treatments for this high-risk group. A study from the United States further illuminates this issue, reporting that 56% of individuals attempting suicide within 12 months had sought psychiatric services, yet half of them perceived unmet treatment needs [9].

Skogman et al. [10] conducted interviews with individuals who had previously attempted suicide. The authors underscored the importance of addressing patients’ desires for enhanced self-understanding, acquisition of problem-solving skills, improved help-seeking behaviors, and assistance with social and economic challenges. These identified needs align with resources such as psychotherapeutic interventions and multidisciplinary support systems. In a one-year follow-up, Cedereke et al. [11] investigated the needs of suicide attempt survivors. The authors concluded that post-attempt needs encompassed not only health-related aspects but also fundamental psychosocial needs, with social needs becoming more pronounced than psychiatric needs after a year. Synthesizing these insights, it becomes evident that suicide attempt survivors require a flexible, long-term follow-up strategy tailored to address a diverse array of needs.

Today, it is common practice in psychiatric services to document the grading of an individual’s suicide risk as an attempt to predict future suicide attempts or suicides, but such traditional suicide risk assessments lack clear scientific support [12]. Hawton and colleagues have proposed that instead of attempting to predict the risk of suicidal behavior, all patients with mental health problems should be considered potentially at increased risk of suicide, and tailored planning should be developed to manage each patient’s suicide risk [12]. This planning would involve not only assessing and summarizing the patient’s condition and suicide risks but also safety planning to prevent suicide attempts and other risk-reducing interventions such as contact with the appropriate healthcare provider, treatment, and psychosocial measures. There are various methods of safety planning [13] and research is ongoing regarding their evidence base and optimal utilization [14].

A recent comprehensive review encompassing 18 studies on psychotherapeutic interventions for suicide attempters found that Cognitive-Behavioral Therapy (CBT)-related and potentially psychodynamic approaches demonstrated efficacy in preventing subsequent suicide attempts [15]. This corroborates findings from a previous review [16] emphasizing that interventions should explicitly target suicidal behaviors/episodes rather than solely addressing symptoms of psychiatric disorders. Considering these findings, a pressing need for novel interventions emerges, tailored to the unique challenges faced by the group of high-risk individuals who have attempted suicide.

The Attempted Suicide Short Intervention Program (ASSIP), developed by suicide researchers [name] and [name] in Switzerland, emerges as a promising psychotherapeutic strategy for suicide prevention [17]. ASSIP includes a concise three-session format as an adjunct to standard care. Rooted in attachment theory, action theory, and cognitive theory, ASSIP recognizes the comprehensibility of patients’ actions through the lens of their life history, individual vulnerabilities, life goals, and basic needs. The intervention is designed to address the unique needs of each patient, supporting both short and long-term goals and structured as an add-on to regular treatment. The initial ASSIP session involves a narrative interview, videotaped for subsequent review. The second session includes video playback, enabling the patient and therapist to analyze and enhance the information jointly. Homework involves reading and commenting on a psychoeducational text covering themes that have been identified as relevant for understanding the background of suicide attempts in previous research. The third session involves the creation of a written case formulation, identifying individual vulnerabilities and the precipitating events leading to the suicidal crisis. Collaboratively, patient and therapist develop personalized suicide prevention measures. Long-term suicide prevention strategies, generated through individual analysis, may involve continued healthcare contact, including pharmacological and psychotherapeutic treatment. As part of the intervention, standardized letters from the therapist are sent to the patient over two years, to reinforce safety strategies, and offer support during potential crises.

In a randomized controlled trial (RCT) conducted in Switzerland [17], 60 patients receiving ASSIP in addition to standard care exhibited an 80% risk reduction for new suicide attempts within two years compared to the control group. Health economic benefits were observed [18]. However, a Finnish study [19] comparing ASSIP with crisis intervention demonstrated no discernible difference in effectiveness, which the authors potentially attributed to methodological limitations and the high prevalence of personality disorders among participants [19]. A small pilot RCT from the US [20] focusing on individuals with extensive substance abuse problems and suicide attempts, reported no difference in repeated suicide attempts but a reduction in suicidal thoughts with an adapted form of ASSIP treatment compared to standard care. Notably, the healthcare context appears to influence intervention outcomes. While ASSIP displays promising results, replication studies in diverse international contexts are hindered by methodological challenges. Comprehensive investigations, encompassing treatment fidelity, usual care content, and patient selection criteria, are warranted to determine the effectiveness of ASSIP in preventing new suicidal behaviors.

## Method

### Aims

In response to the scarcity of studies focusing specifically on psychotherapeutic interventions for individuals who have attempted suicide, our research endeavors to evaluate the efficacy of the Attempted Suicide Short Intervention Program (ASSIP) when implemented in psychiatric services for recent suicide attempters in Sweden. This paper outlines the study’s design and planned assessments, aiming to address key research questions.

Primary research questions include:

Efficacy of ASSIP: Does the incorporation of ASSIP into standard treatment effectively prevent new suicide attempts in individuals with a recent attempt compared to standard care only?

Identification of moderators and mediators: Can potential moderators or mediators associated with the efficacy of ASSIP be identified, contributing to a nuanced understanding of its impact?

Specific Patient Groups: Does ASSIP demonstrate efficacy in preventing new suicide attempts within specific patient groups, such as those diagnosed with depression, individuals with no attempt prior to the index attempt, or those who have made a serious suicide attempt?

Reduction of Self-Stigma: Does ASSIP contribute to a reduction in self-stigma among individuals who have attempted suicide?

Cost-effectiveness: Is the addition of ASSIP to conventional treatment cost-effective when compared to standard care?

Preliminary side projects include:

Self-Stigma Investigation: An exploration of self-stigma among suicide attempters, with a focus on assessing the potential impact of ASSIP on individuals’ experiences of stigma.

Coping Strategies Analysis: An investigation into coping strategies employed by suicide attempters, examining the correlation with stressful life events and exploring the potential influence of ASSIP on coping styles.

Adherence Scale Development: The development of an adherence scale to assess the extent to which ASSIP therapists adhere to the ASSIP manual, ensuring consistency and fidelity in the intervention’s implementation. Investigation of possible associations between adherence to the method and treatment outcome.

Mechanism of change within the ASSIP intervention: Investigation of whether the long-term therapy goals of the ASSIP conceptualization have been addressed and whether addressing these goals during follow-up impacts the primary and secondary outcome measures.

### Study design and data management

The study is an RCT. Patients are randomized to either receive ASSIP + usual treatment or only usual treatment. The project employs stratified randomization based on the study site, ensuring that 50% of patients receive ASSIP at all sites. Randomization occurs electronically at the end of visit 1 via REDCap and is blinded to the data handler. REDCap is an electronic data capture tool [21] hosted at Lund University which will be used to manage data collection. The participating regions will collectively recruit a total of up to 460 patients who have recently attempted suicide. For this study, a suicide attempt is operationally defined as a self-inflicted, potentially harmful behavior exhibiting explicit or implicit evidence of the individual’s intent to die [22].

